## Abstract

**Background:**

Besides cognitive decline, Alzheimer's disease (AD) leads to physical disability, need for help and permanent institutional care. The trials investigating effects of exercise rehabilitation on physical functioning of home-dwelling older dementia patients are still scarce. The aim of this study is to investigate the effectiveness of intensive exercise rehabilitation lasting for one year on mobility and physical functioning of home-dwelling patients with AD.

**Methods:**

During years 2008-2010, patients with AD (n = 210) living with their spousal caregiver in community are recruited using central AD registers in Finland, and they are offered exercise rehabilitation lasting for one year. The patients are randomized into three arms: 1) tailored home-based exercise twice weekly 2) group-based exercise twice weekly in rehabilitation center 3) control group with usual care and information of exercise and nutrition. Main outcome measures will be Guralnik's mobility and balance tests and FIM-test to assess physical functioning. Secondary measures will be cognition, neuropsychiatric symptoms according to the Neuropsychiatric Inventory, caregivers' burden, depression and health-related quality of life (RAND-36). Data concerning admissions to institutional care and the use and costs of health and social services will be collected during a two year follow-up.

**Discussion:**

To our knowledge this is the first large scale trial exploring whether home-dwelling patients with AD will benefit from intense and long-lasting exercise rehabilitation in respect to their mobility and physical functioning. It will also provide data on cost-effectiveness of the intervention.

**Trial registration:**

ACTRN12608000037303

## Background

Dementia is the most important disease group leading to disability and requiring social and health care among older individuals [1]. The most prevalent of dementing illnesses (55-80%) is Alzheimer's disease which leads to gradual and often steady decline of cognitive functioning, to various behavioural and psychological symptoms and physical disability [2]. Disabilities lead to loss of autonomy, require help and support as well as institutional care. Dementia with its consequences is also very expensive for the society [1].

One pivotal problem in dementia leading to need for help and institutional care is decline in mobility. Locomotion gets stiff, walking decelerates and falls are common [3]. The stiffness and emerging disabilities makes caregivers' work demanding. Going outdoors, getting dressed and undressed as well as transfers from one place to another become challenging [1]. This process is accelerated by patient's progressive sarcopenia, weight loss and muscular weakness which impede body control and predisposes to falls [4].

Some earlier studies have suggested that physical exercise may be beneficial in dementia. Physical activity and regular exercise training may slow down cognitive decline [5,6], and it has positive effects on cognition among those with cognitive decline [7]. Exercise alleviates depression and reduces behavioural symptoms in dementia patients [7,8]. There are several controlled trials testing effectiveness of endurance or strength training among patients with dementia or in samples with a large proportion of patients with dementia. Most of the trials have a low number of participants and, therefore, low power to show effectiveness. In addition, many of the trials are not randomized. A meta-analysis of these trials showed a small but significant effect on strength and endurance outcomes [9]. Majority of these trials have been performed in nursing homes or in long-term care. One randomized study in a nursing home setting has shown that intensive, long-lasting exercise training may even improve physical functioning of Alzheimer's patients [10]. According to the trials showing effectiveness on physical functioning, the training program should be intensive, long-lasting and versatile.

We found only four clinical exercise trials targeted on home-dwelling patients with dementia [8,11-13]. Three of them were performed with very low number of patients (N = 29-81) [11-13] and two of them did not show any effectiveness [11,12]. Teri's study [8] was targeted to improve behavioural symptoms in dementia. Thus, there are still only few rigorous randomized trials investigating the effectiveness of physical rehabilitation among home-dwelling patients with dementia. Although some studies have shown promising effects of exercise on physical functioning among institutionalized patients with dementia, there are no such studies among home-dwelling patients with Alzheimer's disease (AD).

We are testing intensive exercise training performed twice weekly either at patient's home or in a day centre and lasting for one year on patients Alzheimer's disease (AD). The primary aim of this study is to investigate the effects of exercise on AD patients' mobility and physical functioning. The secondary aims are to assess the effects of exercise interventions on patients' neuropsychiatric symptoms and cognition. We also investigate the effects of intervention on the use and costs of health care services, admissions of AD patients to permanent institutional care (cost-effectiveness), falls and mortality. The effects on the caregivers' quality of life will also be assessed.

## Methods

### General design

This is a multicenter, controlled intervention trial with a prospective, randomized design. The aim is to study the effects of two exercise interventions, one performed at AD patients' home for one hour twice a week, and another performed at rehabilitation day centres for four hours twice a week. The interventions will last for one year, and they are compared with usual care. The study has been approved by the Ethics Committee of the Helsinki University Central Hospital. Informed consent has been obtained from each patient and/or their spousal caregiver before any study procedure which are performed according to good clinical practice. An executive committee ([name], [name], [name]) is responsible for the planning, conduct and monitoring of the study.

### Participants

The study was started in 2008 by posting a letter to a random sample of patients receiving reimbursement for AD medication according to the centralized Drug Imbursement Register of the Social Insurance Institution of Finland (Kela), and his/her spouse living at the same address. All these patients had undergone detailed diagnostic assessments before acquiring reimbursement for their AD medication (e.g. cognitive and neuropsychological tests, neuroimaging and laboratory tests). The outline of the exercise study was described, and they were invited to participate.

Besides AD and spouse requirement, the inclusion criteria are:

- living in the greater Helsinki area (Helsinki - Espoo - Vantaa)

- age over 64 years

- no terminal disease, no severe hemiparesis

- independent mobility - with walking devices if needed

- frailty: at least one fall during last year, slowed walking speed, or weight loss during one year

All the spouses of the AD patients showing interest in participation are sent a questionnaire to confirm the fulfilment of the inclusion criteria and they are further interviewed via telephone about the frailty criteria, mobility and diseases. Those couples fulfilling inclusion criteria are invited for the first study nurse visit. At the beginning of the first visit the couples are given written and oral information of the study and they are asked to sign an informed consent. Both patients and their spousal caregivers give consent. In case of the AD patient's poor capability of judgement the spousal caregiver gives proxy's consent for both spouses.

### Study procedures

The baseline study visit lasts about two hours and includes interview of both spouses' demographic data, diagnoses, medications used, and baseline use of health and social services. The diagnoses and medications are confirmed from medical records provided by the couples. Charlson comorbidity index is calculated to assess the severity and prognostic value of the participants' disease burden [14].

The AD patients are assessed by Clinical Dementia Rating Scale (CDR) [15], Minimental State Examination (MMSE) [16], verbal flow [17,18], clock drawing test [19], Mininutritional Assessment (MNA) [20], Neuropsychiatric Inventory (NPI) [21,22], Cornell depression test [23], mobility tests and balance tests [24], and the Functional Independence Measure (FIM) [25]. Patients' weight, blood pressure (with 10 min rest and recorded in a sitting position), heart rate and handgrip strength [26] are assessed on each visit. Falls and fractures are recorded with the aid of diaries kept by caregivers and recorded on each visit.

The spousal caregivers are assessed by the Zarit burden scale [27], Geriatric Depression Scale (GDS) [28], RAND36 [29,30] and mobility and balance tests [24]. At six months the caregivers are asked to give feedback for the study and their satisfaction is assessed.

The couples are randomized in clusters of 30. After assessing 30 couples with eligibility and frailty criteria confirmed and agreeing to consent the study, the randomization is performed. Couples are randomly allocated by means of computer-generated random numbers to three arms: to receive home rehabilitation, day care rehabilitation or to receive the usual care. The study nurse calls by telephone to a randomization staff member who has not seen the couples neither their clinical records. She assigns the next number from the computer and the group assignment to the patient.

Participating couples are assessed by two study nurses four times during the year: at baseline, and at 3, 6, and 12 months. In addition, those remaining in the community will be invited for a follow-up visit at 24 months. The study assessment procedures are described in table 1. Use of health and social services, institutionalizations and death dates on both the patients and the caregivers will be retrieved from the central registers until two years from baseline measurements.

**Table 1 T1:** Study assessment procedures and timetable.

Assessment^1^	Telehone interview	Baseline visit	3 month visit	6 month visit	12 month visit	24 month visit

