#### Intervention

A geriatrician performs comprehensive geriatric assessment prior the intervention and makes the rehabilitation plan including also nutritional care.

1. Home-based physical exercise and rehabilitation procedures (one hour twice a week for 12 months) are performed by physiotherapy professionals of an expert organization (Suomen Fysiogeriatria), with long-term experience of dementia exercise rehabilitation. Interventions are tailored according to the patient's and caregiver's needs (for example: training transfers, stair climbing, balance training, executive functioning or dual-tasking).

2. Day rehabilitation centre-based physical exercise and rehabilitation (4 hours twice a week for 12 months) is organized and performed by professionals of dementia physiotherapy at two day rehabilitation centres (with gym and experience) performing the day care rehabilitation. Intervention consists of endurance, balance, and strength training as well as dual task training and exercises directed to improve executive functioning. Taxi transportation and lunch are provided for participants during the intervention days.

The intervention is provided up to one year or until patient is admitted to permanent institutional care.

Patients randomized to the control group receive the usual care in normal health care system, but they are provided with oral and written advice on nutrition and exercise by the study organization.

As a nutritional advice, all patients receive advice to ensure a sufficient intake of energy and protein [4] and to take 20 μg of vitamin D supplements per day [31].

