### Outcome measurements

Primary outcome measures are changes in patients' mobility assessed by the tests described by Guralnik et al [24] and in physical functioning according to the FIM measure [25].

Secondary outcome measures are changes in patients' cognition by verbal flow [17] and MMSE [16], neuropsychiatric symptoms by NPI [21,22] and Cornell [23], number of falls, and permanent institutionalizations and time spent at home. Changes in caregivers' satisfaction, burden by the Zarit burden scale [27], depression by the GDS [28], health-related quality of life by the RAND-36 [29,30] will be measured as secondary outcomes.

Total mortality, use and costs of health and social care services of both spouses as well as cost-effectiveness of the intervention will be measured up to 24 months from the beginning of the baseline measurements.

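### Register, mortality and cost outcomes are counted from baseline although couples are allocated only once a batch of 30 has been assessed, so the 24-month window includes time before randomisation

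*Protocol article*

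**What the plan says.** Order of events (protocol article, Participants and Study procedures). Consent is sought when a couple is first seen: "At the beginning of the first visit the couples are given written and oral information of the study and they are asked to sign". Allocation comes later and in batches: "The couples are randomized in clusters of 30", and "After assessing 30 couples with eligibility and frailty criteria confirmed and agreeing to consent the study, the randomization is performed". A couple counted towards the 30 has therefore already been seen and has consented.

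Clock for the register outcomes. Study procedures says that service use, institutionalisations and deaths "will be retrieved from the central registers until two years from baseline measurements". Outcome measurements says that mortality, service use, costs and cost-effectiveness "will be measured up to 24 months from the beginning of the baseline measurements". Both passages name baseline as the origin, not randomisation.

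Clock for the clinic visits. Couples are assessed "four times during the year: at baseline, and at 3, 6, and 12 months", with a further visit at 24 months. The article does not say from which date the months are counted. On treatment, Intervention says: "The intervention is provided up to one year or until patient is admitted to permanent institutional care". It does not tie the start to baseline or to randomisation.

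**The concern.** The arms can differ only from allocation onwards. If the clock starts at baseline and allocation waits for the batch to fill, the early part of each couple's window holds service use and costs that cannot be an effect of the intervention. Because the window has a fixed length, the same number of months is lost at its far end.

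This matters most for cost-effectiveness, which the Discussion section of the abstract presents as one of the trial's products. Service use and costs gain variance unrelated to treatment, and all register outcomes have less real follow-up than the nominal 24 months. The direction is towards finding no difference.

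**Working it through.** **The plan's own figure.** Statistical analyses gives SD 20, a 10-point FIM difference, 5% type I error and 80% power. With a two-sided test, n = 2 × (1.960 + 0.842)² × 20² / 10² = 62.8, so 63 per group. Then 63 / 0.90 = 70 per group, and 3 × 70 = 210. The figure reproduces and this point does not change it; 210 is needed below as the number of couples to accrue.

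**Inputs**
- Batch size 30 (Study procedures), so 210 / 30 = 7 batches.
- Window of 24 months from baseline (Study procedures; Outcome measurements).
- Accrual period T: not stated exactly. The abstract gives 2008-2010, which as a recruitment period is 24 to 36 months. The same sentence also covers the year of treatment, so accrual could be as short as 24 − 12 = 12 months. I use 12 to 36.
- Assumption: couples arrive evenly.

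**Formulas.** Rate r = 210 / T couples per month. Within a batch, couples wait for 0, 1, …, 29 further arrivals. The mean wait is therefore 14.5 / r and the longest 29 / r. The share of the window is wait / 24.

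| T (months) | r per month | Time to fill a batch, 30 / r | Mean wait (share of 24) | Longest wait (share of 24) |
|---|---|---|---|---|
| 12 | 17.50 | 1.71 | 0.83 (3.5%) | 1.66 (6.9%) |
| 24 | 8.75 | 3.43 | 1.66 (6.9%) | 3.31 (13.8%) |
| 36 | 5.83 | 5.14 | 2.49 (10.4%) | 4.97 (20.7%) |

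**Follow-up left after allocation.** On average 24 − 0.83 = 23.2 down to 24 − 2.49 = 21.5 months. For the first couple in a batch, 24 − 1.66 = 22.3 down to 24 − 4.97 = 19.0 months.

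**What this does to a cost contrast (illustration).** Suppose monthly cost is c in the control arm and c − d in an intervention arm from allocation onwards, both constant. With a wait w, the totals over the stated window are 24c and 24c − d(24 − w). The difference is d(24 − w) instead of 24d, so both the absolute and the relative contrast shrink by w / 24. At the mean wait that is 3.5% to 10.4%. If the difference arises mainly during the treatment year, the absolute loss is smaller.

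**The case against.** The strongest reply is that the effect is modest, even-handed and confined to non-primary outcomes. Waiting time is unrelated to arm because whole batches are allocated at random. Pre-allocation costs are equal in expectation, so by themselves they add variance without shifting the absolute difference. Even with a 5-month wait, the window could hold a full year of treatment from allocation plus about 7 months (19.0 − 12). The article gives no waiting time, and recruitment by posted letter lets the team fill a batch quickly. All of this stands and limits the size of the point. It does not remove it, because the origin is stated twice and allocation follows assessment by rule.

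A second reply is that index dates belong in a fuller document. That would answer a missing date, but here the article states one.

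Four stronger readings are tempting and are not supported:
- **The primary outcomes are diluted and power for FIM and mobility falls.** The visit list starts at baseline, and Table 1 places the register items under the same month columns, so a reader might infer that visits run from baseline too. The text does not say so. A power figure would need that reading, an assumed wait and an effect growing linearly with exposure. If visits run from randomisation, exposure at 12 months is not shortened; the baseline value is merely older. If the effect plateaus early, the loss at 12 months could be near zero.
- **Some 3-month visits precede allocation.** This requires visits timed from baseline and slow accrual. With 12 months' accrual the longest wait is 1.7 months, so it could not happen.
- **Untreated deaths enter the mortality comparison.** A patient who dies while waiting would presumably not be allocated, so among randomised patients the wait is free of deaths. Much the same applies to institutionalisation, since the trial enrols home-dwelling patients. For these outcomes the cost is shorter follow-up, not added events.
- **One arm is favoured.** Nothing in the procedure would do that.

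**Conclusion.** The point holds for the register, mortality and cost outcomes. Followed as written, the plan counts time before allocation in the 24-month window for all but the last couples in each batch. The consequences are extra variance in service use and costs, less post-randomisation follow-up for every register outcome, and contrasts drawn somewhat towards no difference.

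Under even accrual over 12 to 36 months, the share of the window affected averages 3.5% to 10.4% and reaches 6.9% to 20.7% for the first couple in a batch. These figures rest on the accrual assumption alone; recruitment in quick waves would make them smaller. The plan's sample size is unaffected. For FIM and mobility the most that can be said is that the origin of the visits should be stated.

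**What to change.** In Study procedures and Outcome measurements, replace baseline by the date of randomisation as time zero for service use, costs, cost-effectiveness, institutionalisation and mortality. Follow each couple for 24 months from that date, and exclude service use and costs incurred before it. State that the 3, 6, 12 and 24 month visits are timed from the same date, so that clinic and register data share one clock. Report the observed interval from baseline to randomisation, so that readers can see how old the baseline values are.

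The cost is a change of wording and a new index date in the register extraction. Each couple's register window would close about 0.8 to 2.5 months later on average, and 1.7 to 5.0 months later for the first couple in a batch. Sample size and allocation procedure stay as they are.

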### Intervention

A total of 210 patients will be randomized in three groups (70 per each arm) as follows:

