### Statistical analyses

Sample size was calculated based on the FIM measure [25]. With an estimated standard deviation 20, and type I error 5%, 80% power, 63 patients would be needed in each group to show a 10-point difference between groups. With estimated 10% drop outs in each group about 70 patients are needed in each group. Data will be analyzed on intention-to-treat basis. Imputation method "the last observation carried forward" (LOCF) and "Worst-rank score"-principle will be used.

In these baseline findings, for the continuous variables, descriptive values were expressed by means with standard deviations (SD) and medians with range. For the variables with a normal (Gaussian) distribution, statistical comparisons between the groups are made by using an analysis of variance. If the variables have a non-normal distribution or ordinal level, statistical comparison between groups was made using the Kruskall-Wallis test. Measures with a discrete distribution were expressed as percentages (%) and analysed by Chi-Square or Fischer's exact test when appropriate.

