## Discussion

This trial investigates the effects of intense, long-lasting physical exercise on home-dwelling patients with AD. It has two active intervention arms which are compared with usual care. One third of patients receive home-based tailored exercise twice a week one hour at the time for one year or until the patient is admitted to permanent institutional care. Another third of patients are receiving versatile exercise training including endurance, balance, and strength training as well as dual task training and exercises directed to improve executive functioning. This intervention is provided in day centers for four hours/day twice weekly for one year or until the patient is admitted to permanent institutional care.

There are several strengths in our study. All participants have an established diagnosis of AD because all are recruited from the drug register. This register requires definite diagnosis based on cognitive tests, disability, laboratory tests, and CT scan or MRI scan for the AD drug reimbursement. All participants suffer from frailty, and have therefore a need for exercise rehabilitation. Thus, the findings should be applicable in real life. The exercise training is intense and long-lasting, thus, reinforcing effectiveness of the intervention. The used resources and costs will be counted in detail.

However, there are also several challenges in this study. First, the population is old and frail with many comorbidities, and, thus, vulnerable to competing causes of complications and deaths. The second challenge relates to a sufficient difference to be attained between the groups with our intervention. Contamination of the control group is probably not a problem, because exercise rehabilitation is rarely available for dementia patients in Finland unless they are the Second World War veterans [32], in practice over 83 years of age in 2008. Although the FIM has been developed to measure outcomes of rehabilitation and validated among very old patients [25], it is not very clear how the FIM measure will respond to change in functioning as a consequence of exercise intervention in patients with AD. It was also challenging to find suitable scales to measure change in cognition in this heterogeneous group consisting of all stages of dementia.

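### Dementia stage is known before each batch of 30 couples is randomised, but the allocation described does not use it: valid, yet it leaves avoidable chance imbalance and loses some precision

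*Protocol article*

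**What the plan says.** The inclusion criteria (Protocol article, Methods, Participants) cover age, residence, mobility, frailty and the absence of terminal disease or severe hemiparesis. None of them limits CDR or MMSE. The Discussion confirms the breadth of the population, calling it "this heterogeneous group consisting of all stages of dementia".

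CDR is taken at the baseline visit (Study procedures and Table 1). Randomisation follows once 30 couples have been assessed, found eligible and have consented. The allocation is then described: "Couples are randomly allocated by means of computer-generated random numbers to three arms". The study nurse telephones a staff member who has seen neither the couples nor their records, and "She assigns the next number from the computer and the group assignment to the patient". No stratum or minimisation factor is named.

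The sample size rests on FIM and a target difference of 10 points: "With an estimated standard deviation 20, and type I error 5%, 80% power, 63 patients would be needed in each group". The Intervention section plans 210 patients, 70 per arm.

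**The concern.** Stage of dementia plausibly relates to baseline function, rate of decline and risk of institutional care. An arm that by chance receives more moderate or severe patients may decline faster for reasons unrelated to exercise. That would touch both primary outcomes and time spent at home, and with two active arms compared with one control there are two chances for it to happen.

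The usual practical obstacle to stratifying, that patients arrive and are randomised one at a time, is absent here. The trial already holds 30 couples with their CDR on file before any of them is allocated. What is at stake is precision and the credibility of the comparison, not its validity.

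**Working it through.** **1. The plan's own figure.** Inputs from Statistical analyses: difference 10, SD 20, type I error 5% (two-sided reproduces the figure), power 80%.

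- n per group = 2 × (1.960 + 0.842)² × 20² / 10² = 62.8, so 63, as stated.
- 63 / 0.90 = 70 per arm, and 3 × 70 = 210, as stated.
- Standard error of a contrast = 20 × √(2/63) = 3.56 FIM points.

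Nothing in this point disputes these numbers.

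**2. Chance imbalance in stage.** Let p be the share of patients at CDR 2-3. The article does not give p, so 20% to 50% is an assumption. The SD of the between-arm difference is √(2p(1−p)/70). The probabilities below come from simulating independent counts of 70 per arm, and they refer to at least one active arm differing from control. They are counted in whole patients: 10 points is exactly 7 of 70, and 15 points requires 11 of 70.

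| p | SD of difference | ≥10 points | ≥15 points |
|---|---|---|---|
| 20% | 6.8 points | 28% | 5% |
| 30% | 7.7 points | 38% | 9.5% |
| 40% | 8.3 points | 42.5% | 12.4% |
| 50% | 8.5 points | 44% | 13.5% |

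**3. What an imbalance does to the FIM contrast.** Shift = imbalance × gap in 12-month FIM change between CDR 2-3 and CDR 0.5-1. The gap is not in the article; 10 to 20 points is an assumption.

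- 15-point imbalance: 0.15 × 10 = 1.5 and 0.15 × 20 = 3.0 FIM points, or 0.42 and 0.84 of the standard error of 3.56.
- Imbalance of one SD at p = 40%: 0.083 × 10 = 0.8 and 0.083 × 20 = 1.7 points.

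**4. What using stage would gain.** If the SD of 20 describes the quantity analysed in the enrolled population, stage explains p(1−p) × gap² / 20² of the variance. At p = 40% this is 0.24 × 100/400 = 6% for a 10-point gap and 0.24 × 400/400 = 24% for a 20-point gap. With a share R² explained and stage used in the analysis, the residual SD is 20 × √(1−R²). At 63 per group:

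| R² (assumed) | Standard error | Power |
|---|---|---|
| 0 | 3.56 | 80.1% |
| 5% | 3.47 | 82.1% |
| 10% | 3.38 | 84.1% |
| 20% | 3.19 | 88.1% |
| 30% | 2.98 | 91.8% |

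**5. A secondary and conditional matter: order of the calls.** Seven batches of 30 giving 70 per arm would fit a 10:10:10 split within each batch, but the article does not state one, nor the order in which couples are called in. If batches were so balanced, the expected number of final allocations already determined would be 1 + 9/29 + (9/29)(8/28) + … = 1.43 per batch, or 7 × 1.43 = 10 of 210.

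**The case against.** The strongest reply is that nothing here is an error. Unstratified randomisation of 70 per arm, done after consent and baseline assessment by someone who has not seen the records, is sound. Chance imbalance is part of ordinary sampling error. The planned SD of 20, if it is meant for the enrolled population, already contains the variation between stages, so the shifts in step 3 lie inside the standard error and are not additional to it. This stands in full.

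Three further limits also stand. The primary outcomes are changes, which removes part of any baseline difference. Independent mobility and living with a spouse probably keep the number of severe cases down. The CDR mix and the FIM gap are assumptions.

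It can also be said that a condensed article may omit a stratum that the full protocol contains, and that adjustment belongs in the analysis plan. That is partly right. The article does not say outright that stage is ignored; this is inferred from an allocation procedure in which no step uses it. The tests named under Statistical analyses are written for the baseline findings, so they do not show that the outcome comparisons omit stage. What remains is a described allocation step that can be improved at little cost.

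A reader might infer that the results will be biased, or that the false-positive rate is inflated. The documents support neither. A reader might also infer that the nurse can steer couples into arms. That would need balanced batches, a free call order and someone tracking the allocations, and the article states none of these. All 30 couples have already been assessed and have consented, so at most the order of a few last calls could be influenced.

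**Conclusion.** The point holds as a cheap design improvement, not as a fault in validity. The trial enrols all stages, has CDR in hand before each batch is randomised, and describes an allocation that makes no use of it. Under an assumed 30% to 50% at CDR 2-3, an imbalance of 10 points or more against control in at least one active arm is common, and one of 15 points or more is uncommon but not rare. At a 20% share both are less frequent.

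The effect on the FIM contrast is modest. It stays below one standard error even with a 15-point imbalance and the largest assumed gap. Reading 1.5 to 3 points as 15% to 30% of the 10-point target is arithmetically correct, but it would suggest a distortion on top of the planned uncertainty, which it is not. The loss is some precision, and a baseline table that may be hard to defend if the arms differ visibly in stage. The predictability of the last calls is only a conditional remark.

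**What to change.** For batches not yet allocated, when 30 couples are complete, send the randomisation office one fixed, numbered list giving each couple's baseline CDR group (0.5-1 versus 2-3). Allocate the whole list in one step, stratified by CDR group, and return all 30 allocations together. This also removes any question about call order.

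For all batches, including those already allocated, include baseline CDR group as a factor in the outcome comparisons, and specify this before outcomes are compared. The article already reports baseline methods in the past tense, so many batches may have been randomised; this second part is useful however many remain. If the full protocol already stratifies by stage, a sentence saying so is enough.

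The cost is a changed allocation script and one list per batch instead of separate telephone calls. Arm sizes within a batch may differ by a couple or so. The planned 63 evaluable and 70 randomised per arm do not change, and no new measurement is needed.
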